## Abstract

**Introduction:**

Imbalance of the gut microbiome is key to the pathogenesis of ulcerative colitis (UC). Faecal microbiota transplant (FMT) is the transfer of homogenised and filtered faeces from a healthy individual to the gastrointestinal tract of a patient with disease. Published datasets show a positive signal for the use of FMT to treat UC, but the optimal route and dose of FMT remain unanswered.

**Methods and analysis:**

This prospective, multi-centre open-label, randomised pilot study will assess two possible routes of FMT delivery, via the nasogastric (NG) route or by delivery to the COLON, in 30 patients with active UC recruited from three sites in the UK. Stool will be collected from healthy screened donors, processed, frozen and stored under a Medicines and Healthcare products Regulatory Agency (MHRA) “specials” manufacturing licence held at the University of Birmingham Microbiome Treatment Centre. Thawed FMT samples will be administered to patients either via eight nasogastric infusions given initially over 4 days starting on the day of randomisation, and then again for 4 days in week 4 for foregut delivery (total of 240 g of stool) or via one colonoscopic infusion followed by seven weekly enemas according to the hindgut protocol (total of 360 g of stool). Patients will be followed up weekly for 8 weeks, and then at 12 weeks. The aims of this pilot study are (1) to determine which FMT administration route (NG or COLON) should be investigated in a randomised double-blind, placebo-controlled trial and (2) to determine if a full randomised controlled trial is feasible. The primary outcome will be a composite assessment of both qualitative and quantitative data based on efficacy (clinical response), acceptability and safety. At the end of the pilot study, decisions will be made regarding the feasibility of a full randomised double-blind, placebo-controlled trial and, if deemed feasible, which route of administration should be used in such a study.

**Ethics and dissemination:**

Ethical approval for this study has been obtained from the East Midlands-Nottingham Research Ethics Committee (REC 17/EM/0274). At the end of the study, findings will be reported at national and international gastroenterology meetings and published in peer-reviewed journals.

**Trial registration number:**

ISRCTN74072945

Strengths and limitations of this studyMatching of single donor with each patient—this will allow detailed exploration of donor characteristics associated with a favourable patient response.Intensive faecal microbiota transplant (FMT) treatment regimen—shown to be a major contributing factor in clinical response to FMT.Assessment of mechanistic outcomes and donor diet—this will help in understanding the mechanisms associated with response to FMT.Qualitative data from clinicians and patients informing the potential future randomised controlled trial (RCT).This study is limited to assessing the feasibility of an RCT and the best route of FMT delivery in ulcerative colitis (UC) patients. The assessment of the efficacy of FMT in achieving and maintaining remission for patients with UC needs to be tested in a future full-scale RCT.

## Introduction

In the inflammatory bowel diseases (IBDs), Crohn’s disease (CD) and ulcerative colitis (UC), there is imbalance or 'dysbiosis' of the gut microbiota compared with the healthy bowel, with individuals having IBD showing reduced bacterial diversity compared with healthy individuals.^1 2^Indeed, the currently accepted paradigm concerning the pathogenesis of IBD involves an aberrant immunological response to the intestinal microbiota in a genetically susceptible host.^3^ Whether the observed dysbiosis represents ‘cause’ or ‘effect’ remains unanswered. Faecal microbiota transplant (FMT) is the infusion of a faecal suspension from a healthy donor into the gastrointestinal tract of a patient with disease, and there is interest in the potential of this technique for modifying the gut microbiome as a potential treatment for IBD.^4^

Since the first descriptions of CD and UC at the beginning of the 20th century, it has been strongly suspected that the gut microbiota may have a defining role in the pathogenesis of IBD.^5^ Early culture-based studies underestimated the complexity of the microbiota, and were hampered by various culture biases and the challenge of enumerating fastidious bacteria with complex growth conditions. With the advent of cheap high-throughput genetic sequencing techniques allied with complex bioinformatics capability, there has been a revolution in our understanding of the composition and function of the colonic microbiome. As a result of studies on the microbiome both in patients with IBD and animal models, we know that patients with IBD (either CD or UC) have, at the phylum level, a reduction in Firmicutes and a relative increase in Proteobacteria.^2 6^

Accumulating data suggest that alteration in the gut microbiome plays a central role in driving UC; datasets highlighting the importance of *Roseburia hominis*,^7^
*Faecalibacterium prausnitzii*^8^ and *Akkermansia muciniphila*^9^ mediating anti-inflammatory responses in UC have been published. Attempts to alter the microbiome with probiotics, while disappointing in CD, have shown some promise in UC.^10 11^ Since the first exploratory use of FMT to treat UC in 1989,^12^ numerous case series have been published demonstrating encouraging efficacy signals.^13^ This has led to investigators testing FMT as a treatment for UC and to date there have been four randomised controlled trials (RCTs) of FMT for the treatment of UC.^14^ The first was a trial of fresh and frozen enemas which were delivered weekly for 6 weeks, water being used as placebo.^15^ There was a significant increase in remission at the primary endpoint in the active versus placebo arm. In the second study, fresh FMT by nasojejunal delivery was used and autologous stool was used as placebo.^16^ Although the results favoured active treatment, they were not statistically significant. The last two RCTs were reported in 2017^17 18^and both used frozen FMT from pooled donors and involved intensive treatment regimens. Both achieved statistically significant results in favour of active treatment, with remission rates comparing active and placebo of 32% vs 9%^18^ and 27% vs 8%, respectively.^17^

As a result of this recent work, there is great interest in FMT as a possible treatment for UC, but the optimal route of delivery remains unknown. Before we can undertake a full-scale double-blind RCT of FMT versus placebo, we need to undertake a pilot study to determine the optimum route of FMT delivery and assess the feasibility (recruitment, protocol adherence) of undertaking a trial of FMT in UC. In this pilot study, we will compare nasogastric (NG) versus colonoscopic (COLON) delivery of FMT, using an intensive treatment regimen, in patients with active UC to investigate the optimum route of FMT delivery for the treatment of UC. We will assess the effectiveness and acceptability of the two routes of FMT delivery, and whether FMT by either NG or COLON is suitable to take forward to a full RCT against placebo, and whether such a trial is feasible. Here we describe the protocol for the STOP-Colitis pilot study.

## Methods and analysis

### Study design

A prospective, multi-centre open-label, randomised pilot study to assess two possible routes of FMT delivery for the treatment of UC. Thirty patients with active UC will be randomised to receive FMT via either the NG route or by direct delivery to the COLON. Patients will be recruited from three hospitals in the UK (Queen Elizabeth Hospital, Birmingham; St Mark’s Hospital, London and Glasgow Royal Infirmary).

At the end of the pilot study, the data will be reviewed by an Independent Oversight Committee (IOC), consisting of two consultant gastroenterologists and a professor of medical statistics and clinical trials, who, according to the prespecified STOP/GO criteria (see Analysis of outcome measures below) will decide (1) which route of FMT administration (NG or COLON) is most appropriate to investigate in the full randomised double-blind, placebo-controlled trial and (2) whether it is feasible to proceed to the main RCT.

#### Sample size

As this is a pilot study, no formal sample size calculation was undertaken as the study is not designed or powered to detect a statistically significant difference in efficacy between the two FMT methods of delivery. The recruitment target for this study is 30 patients.

### Aims and objectives

The aims of this pilot study are as follows:

To determine which FMT administration route (NG or COLON) should be investigated in a randomised double-blind, placebo-controlled trial.To determine whether a full RCT is feasible.

In order to achieve these aims, the pilot study has the following clinical (quantitative), qualitative and mechanistic objectives.

#### Clinical objectives

To assess:

Whether FMT by the NG route induces clinical response in patients with active UC.Whether FMT by the COLON route induces clinical response in patients with active UC.Tolerability and safety.Which route of FMT delivery (if any) is suitable to investigate in a RCT.

#### Qualitative objectives

To assess:

Patient acceptability of FMT (NG).Patient acceptability of FMT (COLON).

#### Mechanistic objectives

To assess:

Whether FMT by either route is associated with a change in faecal calprotectin as a surrogate marker of colonic inflammation.Changes in the colonic microbiome and metabolome (short chain fatty acids (SCFA)) induced by FMT via each route.Reduction in C-reactive protein (CRP).

#### Other objectives

Effect of diet (donors) on microbiome.Effect of time from stool donation to treatment on success of FMT.

### Outcome measures

The primary outcome will be a composite assessment of both qualitative and quantitative data relating to efficacy, acceptability, safety and mechanistic outcomes.

#### Clinical outcome measures

Clinical response (primary measure of efficacy) defined as ≥3 point reduction in the full Mayo score from randomisation to week 8, and 30% reduction from randomisation and at least one point reduction of rectal bleeding sub-score or an absolute rectal bleeding subscore of 0 or 1.Time to clinical response (where clinical response is defined as ≥2 point reduction in partial Mayo).Clinical remission at week 8 (full Mayo score of ≤2, with no subscore >1).Participant’s weight at weeks 8 and 12.Quality of Life (QoL) using the generic Short-Form 36 (SF-36) and the disease specific Inflammatory Bowel Disease Questionnaire (IBDQ) at weeks 8 and 12.Adherence to FMT.Adverse events (AE) and serious adverse events (SAE).

### Qualitative data

Patient acceptability will be assessed through qualitative research interviews. During these interviews, patients from both groups will be asked about their perspectives and experience of FMT during the pilot trial, including receiving the intervention, recovering from the intervention and their symptoms and QoL. Further examples of interview questions can be found in the online supplementary file 1.

10.1136/bmjopen-2019-030659.supp1Supplementary data

#### Mechanistic outcome measures

Faecal calprotectin.Measures of microbiome (faecal and mucosal)—specifically shifts in alpha diversity following FMT.Mucosal healing.Urinary metabolome (SCFA).CRP.

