### Mechanistic studies

There will be two aspects to mechanistic studies undertaken as part of this trial; non-invasive assessment of UC activity and assessment of patient’s microbiome response to FMT in comparison with that of donor microbiome at baseline. The study will also investigate donor diet with regard to baseline microbiome and treatment effect.

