#### Microbiome-related assays

#### 16S ribosomal DNA sequencing and metagenomics

16S ribosomal DNA sequencing will be performed on all samples collected during the study: donor faeces (fresh and frozen from day 1 and day 10 donations), faeces from the recipient at baseline, weeks 2, 4, 6, 8, and 12 and mucosal biopsies taken from the right colon, left colon and rectum at baseline and from left colon and rectum at week 8. Together these samples will be compared with clinical data, and correlations found with faecal calprotectin, in order to find the samples most likely to be biologically informative as markers of disease remission. Additionally, and based on the results of the initial 16S analysis, a shotgun metagenomics approach will be undertaken on around 200 selected samples to give insights regarding functional enrichment. For a certain subset of samples where additional strain resolution is required (eg, recovery of complete genomes of interest) or linkage between extra-chromosomal elements such as plasmids and phages, further samples will be subject to long-read sequencing.

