### STOP/GO guidelines

At the end of the pilot, the IOC will be convened to review the data. This group will make a recommendation to the Trial Management Group on (1) which route (if any) of FMT is appropriate to take forward to the full trial and (2) whether it is feasible to proceed to the full RCT.

To determine whether we will proceed forward to the main RCT, a pragmatic review of the pilot data in terms of assessing treatment efficacy (based on clinical response), tolerability and patient acceptability will be undertaken. STOP/GO guidelines will be used to determine whether to proceed forward to the main RCT, and we propose then to take forward the preferred method of FMT delivery into a randomised double-blind placebo-controlled trial with a clinical efficacy outcome (clinical remission).

The first STOP/GO decision will be on which route of FMT to take forward to the full RCT. The pilot is not powered to show differences in the two modes of delivery (NG or COLON); therefore, a decision or recommendation on which route to use in the main trial requires expert judgement and cannot be made based on a purely numerical process. The following data will be reviewed by the IOC:

The proportion of patients who achieve a clinical response following FMT by the NG route (A threshold of achieving a clinical response in around 40% of patients treated may be used. This threshold will be agreed after discussions by the Trial Management Group and the IOC prior to any data analysis being performed).The proportion of patients who achieve a clinical response following FMT by the COLON.Whether FMT by either route is associated with a change in faecal calprotectin.Whether FMT by either route is associated with changes in the colonic microbiome and metabolome.Tolerability and safety for each route.Patient acceptability of FMT by the NG route through the qualitative interviews (including advantages and disadvantages of the NG route).Patient acceptability of FMT by the COLON route through the qualitative interviews (including advantages and disadvantages of the COLON route).

Following review of the above data, whether the IOC can recommend a route to take forward to the main trial, will form the basis of the first STOP/GO decision.

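### The microbiome outcome is narrowed to alpha diversity, which cannot measure the donor-referenced response planned elsewhere and, used alone, can mislead a comparison of routes

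*Protocol article*

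**What the plan says.** Four places in the protocol article bear on what will be measured.

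- Mechanistic outcome measures defines the outcome: "Measures of microbiome (faecal and mucosal)—specifically shifts in alpha diversity following FMT". No other microbiome index is named in the article.
- Mechanistic objectives is wider: "Changes in the colonic microbiome and metabolome (short chain fatty acids (SCFA)) induced by FMT via each route".
- Mechanistic studies describes the assessment as the patient's "microbiome response to FMT in comparison with that of donor microbiome at baseline".
- STOP/GO guidelines puts this item before the Independent Oversight Committee (IOC): "Whether FMT by either route is associated with changes in the colonic microbiome and metabolome". It gives no index, direction or threshold.

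The data would support more than alpha diversity. The section on 16S sequencing covers "donor faeces (fresh and frozen from day 1 and day 10 donations") and "faeces from the recipient at baseline, weeks 2, 4, 6, 8, and 12", plus mucosal biopsies at baseline and week 8. Its stated use of these data is: "Together these samples will be compared with clinical data, and correlations found with faecal calprotectin". It adds that "a shotgun metagenomics approach will be undertaken on around 200 selected samples to give insights regarding functional enrichment", with long-read sequencing where strain resolution is needed. Strengths and limitations states that each patient is matched to a single donor.

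**The concern.** Alpha diversity summarises one sample: how many taxa it holds and how evenly they are spread. Relabelling every taxon leaves it unchanged. A shift in it therefore carries no information on whether the recipient has come to resemble the donor, which is what Mechanistic studies says will be assessed. It is also blind to the phylum-level shifts and named species in the Introduction, although it does address the reduced diversity cited there.

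The outcome list uses a restricting word, so this is a mismatch between stated sections and not merely an index left unnamed. If the one defined measure is what reaches the IOC under its microbiome item, the committee would be comparing two routes on an index that need not order them by how much donor material has taken hold.

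**Working it through.** The article gives no figure for this outcome, so there is nothing to reproduce. The question is what the index can and cannot show. All compositions below are assumed; none are trial data.

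**Definitions.** Shannon diversity H = −Σ p ln p. Bray-Curtis distance to the donor BC = 0.5 Σ|p − q|, where p is the recipient and q the donor. Similarity = 1 − BC.

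**1. Complete replacement at equal diversity.** Recipient (0.4, 0.3, 0.2, 0.1) on four taxa; donor has the same proportions on four different taxa. After full replacement the change in H is 0.00, while BC falls from 1.00 to 0.00.

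**2. No donor transfer.** The same recipient evens out to (0.25, 0.25, 0.25, 0.25) on its own taxa. H goes from 1.28 to 1.39 (+0.11), while BC stays at 1.00.

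**3. Less diverse recipient, as the Introduction expects.** Recipient (0.7, 0.2, 0.05, 0.05), H_r = 0.871. Donor has four other taxa at 0.25 each, H_d = ln 4 = 1.386. With donor share f and no shared taxa,

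H(f) = (1 − f) H_r + f H_d − f ln f − (1 − f) ln(1 − f).

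At f = 0.5: 0.436 + 0.693 + 0.693 = 1.822.

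| Donor share | 0 | 25% | 50% | 75% | 100% |
|---|---|---|---|---|---|
| H | 0.87 | 1.56 | 1.82 | 1.82 | 1.39 |
| BC to donor | 1.00 | 0.75 | 0.50 | 0.25 | 0.00 |

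Full engraftment does register as a rise (1.39 − 0.87 = +0.52), but half engraftment registers as a larger one (1.82 − 0.87 = +0.95). From the formula, H(0.5) exceeds H(1) whenever H_d − H_r < 2 ln 2 = 1.39; here the gap is 0.52. So a donor advantage in diversity does not by itself restore the ordering.

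**4. Larger communities.** Simulation of 2,000 donor-recipient pairs, assuming 400 possible taxa, 120 in the donor, 80 in the recipient, and log-normal abundances with SD 1.5 on the log scale.

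| Donor share | 25% | 50% | 75% | 100% |
|---|---|---|---|---|
| Mean rise in H | +0.59 | +0.80 | +0.78 | +0.38 |
| Mean similarity to donor | 0.31 | 0.54 | 0.77 | 1.00 |

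Half engraftment gave the higher H in about 97% of pairs, and in 93 to 99% when the recipient was given 60 to 120 taxa. In this model taxa are drawn at random, so donor and recipient overlap little. The more they share, the smaller the mixing term and the weaker the reversal.

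**5. Timing of the alternative measure.** Under Interventions, COLON enemas run up to week 7 and the second NG course is in week 4. Time since last FMT is therefore about 8 − 7 = 1 week (COLON) and 8 − 4 = 4 weeks (NG) at week 8, and about 12 − 7 = 5 and 12 − 4 = 8 weeks at week 12. Sequencing detects DNA, so residual donor material could raise week-8 similarity in the COLON arm without engraftment.

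**The case against.** The other side has real points.

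- **The plan is not confined to alpha diversity.** It announces a donor comparison, sequences both parties and provides for strain-level work. This stands. The fault is that the outcome list does not match these sections.
- **Diversity is part of the rationale.** The Introduction opens with reduced diversity in inflammatory bowel disease. This stands, and alpha diversity should be kept.
- **The zero-change case is contrived.** It needs roughly equal diversity in donor and recipient. On the document's own premise full engraftment would on average raise diversity. This stands, so case 1 is possible but not the expected one. It does not answer cases 3 and 4, where diversity rises but out of order with engraftment.
- **The IOC is not tied to this index.** Its item is worded as change in general and is one of seven weighed by expert judgement, and Analysis of outcome measures names clinical response, acceptability and safety as the basis of the decision. This stands and limits the consequence.
- **The choice of index belongs in the full protocol or SAP.** An unnamed index would be no finding in a condensed article. The restricting word in the outcome definition is on the page, however, and conflicts with the other sections.

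A reader might go further and infer that the microbiome input will read as no change under full engraftment, or that the routes will be ranked the wrong way round. The documents do not support either. Nothing in them says that the IOC will see only alpha diversity, and nothing suggests that the arms would divide along the lines of the constructed cases.

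**Conclusion.** The concern holds in a limited form. The outcome definition is narrower than the donor-referenced response in Mechanistic studies and the general microbiome change in Mechanistic objectives and STOP/GO guidelines. Alpha diversity is a valid measure of one stated deficit, but it carries no information on donor likeness and is not monotone in engraftment, so on its own it can favour the route that engrafts less.

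That alpha diversity is blind to donor identity follows from its definition. The size of the reversal (+0.95 at half against +0.52 at full engraftment in the small example; +0.80 against +0.38 in the simulation) depends on assumed compositions with little donor-recipient overlap and is not a prediction for this trial. The likely effect on the route recommendation is modest. The change is still worth making because it costs little and the clinical comparison between routes is not powered.

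**What to change.** In Mechanistic outcome measures, keep the shift in alpha diversity, drop the restricting word, and co-list a second measure: change from baseline in the similarity of each recipient's stool 16S profile to that of the matched donor (for example 1 minus Bray-Curtis or UniFrac distance). Use similarity to donors the patient did not receive as the internal reference. Summarise by route with 95% CI, in line with the no-p-value policy in Analysis of outcome measures.

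Report it at both week 8 and week 12. State that time since last FMT at week 8 differs by route (about one week for COLON, about four for NG), so week-8 similarity alone must not be read as engraftment. The gap between routes is still about three weeks at week 12, but both are then further from their last dose.

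Report both measures to the IOC under the microbiome item in STOP/GO guidelines.

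Cost: outcome and analysis wording and slightly more analysis of sequence data already being generated. No new samples, visits or assays.
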